### Three-month follow up

At three months from baseline, participants in both the PIG and the UCG will be interviewed by telephone to assess their HMR uptake. In addition, participants in the PIG will also be assessed for their experience of the pharmacist-education session about the HMR service. Participants' uptake of HMR will be measured as the proportion of participants who have had at least one HMR since baseline.

### Six-month follow up

At six months from baseline, measures of uptake of HMR will be repeated in participants who have not received a HMR at three months. To ensure reliability, participant self-reported uptake of HMR will be verified with their GP, community pharmacist and/or the pharmacist who undertook the HMR, where possible. The HMR uptake at six months from baseline will be compared between the two study groups.

Participants in both groups will also be asked to complete a questionnaire. Information collected at the six-month follow up will include:

• any changes to medication regimens, including problems experienced with use of medications since baseline;

• medication adherence [11]; and

• health-related quality of life [12].

Data at three and six months will be collected by an independent person who will be blinded to the group allocation.

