### Identification and selection of retirement villages

Retirement villages eligible for the study, such as those with a representative officer (also known as Resident Liaison Officer [RLO]) from the Residents of Retirement Villages Victoria Inc. (RRVV) [10], will be identified in consultation with an officer of the RRVV. Eligible retirement villages meeting the study criteria will be identified by RRVV from their member database. Using the list provided by RRVV, a convenience sample of ten retirement villages will be selected for the study based on the following factors:

• having at least 100 units;

• having at least 20 residents who are members of RRVV; and

• geographical location (northeast and southwest regions).

The two geographical locations will be used to avoid potential contamination (see cluster randomisation). The geographical locations (northeast or southwest) will be randomised to intervention group (Pharmacist Intervention Group [PIG]) or control group (Usual Care Group [UCG]). Each group will include five retirement villages and will have at least 15 km between the PIG and UCG retirement villages. Selected villages should have at least 20 RRVV members to enhance recruitment of participants.

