### Outcome measures and data collection

#### Outcome measures

The primary outcome measure will be participants' uptake of HMR; and secondary outcome measure will be participant self-reported medication adherence. HMR uptake will be assessed at three and six months from baseline, and medication adherence at six months.

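### The three-month follow-up includes questions for the intervention arm only, so the stated blinding of the data collector is not delivered as written

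*Protocol article*

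**What the plan says.** All statements are in the protocol article.

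- **Six-month follow up**, on who collects data: "Data at three and six months will be collected by an independent person who will be blinded to the group allocation". No part of the three-month data is exempted.
- **Three-month follow up**, on the contact made with both arms: "participants in both the PIG and the UCG will be interviewed by telephone to assess their HMR uptake". The next sentence adds: "In addition, participants in the PIG will also be assessed for their experience of the pharmacist-education session about the HMR service".
- **Outcome measures**: "HMR uptake will be assessed at three and six months from baseline, and medication adherence at six months". HMR uptake is the primary outcome.
- **Six-month follow up**, on the second measurement: "measures of uptake of HMR will be repeated in participants who have not received a HMR at three months".
- **Six-month follow up**, on checking the answers: "participant self-reported uptake of HMR will be verified with their GP, community pharmacist and/or the pharmacist who undertook the HMR, where possible".
- **Identification and selection of retirement villages**: "The geographical locations (northeast or southwest) will be randomised to intervention group" or to the control group. Cluster randomisation repeats that whole regions are allocated, not single villages or residents.

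**The concern.** Participants know whether they attended a session, so the trial cannot blind them. The blinded collector is therefore the main safeguard in how the answers are obtained. The three-month task, as described, seems to hand that collector the allocation.

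A collector who knows the arm may explain, probe or accept answers about HMR differently in the two groups. Uptake is the primary outcome and starts as a participant's answer on the telephone, so it is open to this. A reader of the results would also credit the trial with blinded outcome collection that the described procedure does not provide.

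**Working it through.** There is no figure of the plan's to reproduce on this point. The check sets the passages side by side.

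**1. Does the three-month task reveal the arm?** One passage gives all three- and six-month data to a blinded person. Another has both arms telephoned about uptake and adds an assessment for the PIG alone. Whoever puts those extra items to PIG participants must know, by that point at the latest, which participants they are. The article names no other person and no other contact for these items. As written, the two statements do not fit together.

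**2. Would asking about uptake first repair it?** Only in part. With two regions and one arm per region, the first PIG participant identified shows the arm of all five villages in that region, and so of the five in the other. From then on the collector knows the arm before the uptake question is asked. Asking uptake first protects only the earliest calls. This step assumes that the collector can see which village or region a participant lives in, which the article does not state.

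**3. Does it reach the six-month result?** By two routes.
- The wording names a single independent person for both time points. If one individual does both rounds, what was learned at three months carries over.
- Uptake is asked again only of those without an HMR at three months. A three-month answer of yes therefore counts towards six-month uptake without being asked again, unless verification corrects it. This route remains even with a new assessor at six months.

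**4. What does verification do?** GPs and pharmacists can confirm or refute a reported HMR. That can remove false reports after they are made, but it does not change how the answers were obtained. It is promised only when feasible. The article does not say whether answers of no are checked as well.

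**5. Scale.** Nothing in the documents gives a rate of misreporting or an effect of knowing the arm, so no bias can be computed. Only the sensitivity of the outcome can be shown. At the planned 55 per group before inflation, expected numbers with an HMR at six months are 0.03 × 55 = 1.65 in usual care and 0.20 × 55 = 11 in the PIG. One misclassified participant moves an arm's uptake by 1/55 = 1.8 percentage points, against a planned difference of 20 − 3 = 17 points.

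**The case against.** **The conflict is inferred.** The article does not say that the PIG-only items are asked in the same call, by the same person, or before the uptake question. A condensed article may leave call order and staffing to the full protocol. This is fair as far as it goes: a separate contact or a second, unblinded person would remove the conflict. But the article makes a blanket claim of blinding for both time points, describes an arm-specific assessment at one of them, and provides for neither solution. What stands is that certain loss of blinding before each call, or at six months, is not proven.

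**Verification already protects the outcome.** An HMR is initiated by a GP, conducted by an accredited pharmacist and reimbursed to both, so these informants should know whether one took place. This stands as a partial safeguard. A reader might infer that the trial has no protection against biased ascertainment; the documents do not support that.

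**A numerical bias is tempting.** Suppose true uptake is 5% in both arms, with assumed sensitivity of self-report of 95% in the PIG and 70% in usual care. The false difference is then 0.05 × (0.95 − 0.70) = 1.25 points. Adding 3% false positives in the PIG gives (0.0475 + 0.0285) − 0.035 = 4.1 points. With sensitivities of 95% and 50% and 5% false positives, it is (0.0475 + 0.0475) − 0.025 = 7.0 points. The arithmetic is right, but every input is assumed and verification is taken to remove nothing. The figures also describe participants' recall and recognition, which would err even with a perfectly blinded interviewer. They do not measure the effect of an unblinded one. The direction is open as well: education about HMR could reduce false reports rather than create them.

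**Conclusion.** The point holds as an inconsistency in the plan. An assessment confined to the PIG at three months cannot be squared with one blinded collector for all follow-up data unless someone else, or a separate contact, handles it. The article describes neither.

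Loss of blinding at three months follows from the natural reading. Its spread from single participants to whole regions assumes that the collector knows the village or region. Its extension to six-month collection assumes the same individual does both rounds, which the wording suggests but does not settle.

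The resulting bias in uptake cannot be quantified from the documents, and verification limits it to an unknown degree. The text does not support saying that the primary outcome is certainly collected unblinded at both times, or that a given number of points in the result would be spurious. The change is worth making because the outcome is self-reported, few events are expected in usual care, and the remedy costs little.

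**What to change.** 1. Take the education-experience items out of the blinded collector's task. Obtain them on a posted form returned to the study pharmacist or other staff who already know the allocation, or after six-month uptake has been recorded.
2. Use one identical script in both arms that describes an HMR in plain words.
3. Apply the verification already planned in the same way in both arms.
4. Reconcile the sections on three-month and six-month follow-up by stating who asks the PIG-only items and when. If the items stay with the outcome collector, withdraw the blinding statement.

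The cost is a short form, a shared script and a few sentences of text. The downside is slightly later or less complete feedback on the session. Participants may still volunteer that they attended one, so the change removes the disclosure built into the procedure, not every possible one.

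Making provider-confirmed HMRs in all participants the primary outcome would go further. It changes the endpoint, needs confirmation for at least 154 people and requires a rule for missing confirmations. It is open to debate and is not needed to resolve this point.

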### Data analysis

All data will be analysed according to intention-to-treat principles. The baseline characteristics of participants in the PIG and UCG will be compared using Chi-square, Mann-Whitney U or Student t-test. Uptake of HMR in the two study groups at three and six months will be compared using Chi-square test. Paired samples t-test or Wilcoxon Signed-Rank test will be used to compare changes in Morisky scores and SF-12^® ^Health Survey scores between the two groups at six months.

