### Sample size

The sample size required for this study was calculated based on the HMR uptake in the previous 12 months (6%) reported in our recent survey [3]. From this figure, we anticipate the uptake of HMR in the UCG to be 6% after 12 months, 3% after 6 months and 1.5% after three months. To demonstrate that the intervention increases the uptake of HMRs from 3% (in the UCG) to 20% (in the PIG) at six months (considered to be a relatively conservative but clinically meaningful increase), with 80% power and a two-sided alpha value of 0.05, 55 participants will be required in each group (total of 110 participants). Allowing for 20% drop-out or loss to follow-up, and 20% for clustering effects, at least 77 participants will be recruited into each arm at baseline (total of at least 154 participants).

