### Interventions in the Pharmacist Intervention Group (PIG)

At baseline, participants in the PIG will receive the intervention. The intervention to be tested includes several components:

a. HMR education session

• A pharmacist, who is accredited to undertake HMRs, will visit the PIG participants at their villages to deliver a group education session about the role of and benefits from HMR. Information leaflets about HMR will be given out to participants during these education sessions.

b. Medication risk assessment

• A medication risk assessment checklist will be adapted from a screening tool that was previously developed and published by the Pharmacy Guild of Australia (see Additional file 1: Pharmacy Guild of Australia's HMR consumer brochure). The HMR consumer brochure includes a self-administered checklist (with tick boxes) consisting of 16 items assessing a person's risk factors for medication-related problems (e.g. having recent hospitalisation, using multiple medicines, having recent changes to medication regimen, and using low therapeutic index medicines). The checklist will be completed by participants after the education session, with the pharmacist taking them through each question. The completed checklist will be used by the pharmacist to identify participants who have medication risk factors and thus could potentially benefit from a HMR.

c. New referral process for HMR

• Participants identified as having one or more medication risk factors will be referred to their GP. Referral will be made by asking the at-risk participant to give the completed medication risk checklist to their GP during their next GP visit and discuss the need for a HMR.

The group education session, including completion of the medication risk checklist, will take approximately one and a half hours.

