#### Baseline data collection

The baseline characteristics of participants will be collected using a self-completed questionnaire. At baseline, the questionnaire will be sent to participants with the plain language statement and consent form. Information collected by the baseline questionnaire includes:

• demographics;

• medication use data, including medication management and problems experienced with medications;

• medication adherence [11];

• health-related quality of life [12]; and

• medication-related risk factors and eligibility for HMR (see Additional file 1: Pharmacy Guild of Australia's HMR consumer brochure).

Participants' medication adherence will be assessed using the self-reported Morisky scale [11]. The Morisky scale comprises four validated items, with responses to each item scored 0 for 'yes' and 1 for 'no' (except for the item 'Are you always careful in taking your medicines?' where the score is reversed). The total score on the Morisky scale ranges between 0 and 4; a score of less than 4 represents nonadherence.

Participants' health-related quality of life will be assessed using the self-reported Short Form (SF)-12^® ^Health Survey [12]. The SF-12^® ^Health Survey consists of 12 validated items relating to physical and mental health function. Responses to the items will be scored and computed using an online scoring program [13]. The scoring method will give two sets of results - Physical Component Summary (PCS) and Mental Component Summary (MCS) scores, with the scores ranging from 0 to 100, zero representing the lowest level of health and 100 representing the highest level of health [14].

Participants in both groups will be assessed for their medication-related risk factors and eligibility for receiving a HMR using the criteria or items in the Pharmacy Guild of Australia's HMR consumer brochure (see Additional file 1). Participants who fulfil one or more of these criteria will be considered eligible for a HMR.

Participants will be contacted by telephone to obtain incomplete or missing responses.

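### The primary HMR-uptake comparison is unadjusted, so any difference between the two regions in measured HMR risk passes straight into the effect estimate

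*Protocol article*

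**What the plan says.** The Data analysis section of the Protocol article fixes the primary method: "Uptake of HMR in the two study groups at three and six months will be compared using Chi-square test". It names no covariate. Its one stated use of the baseline data is to test the arms against each other: "The baseline characteristics of participants in the PIG and UCG will be compared using Chi-square, Mann-Whitney U or Student t-test".

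Three other sections bear on this.

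- **Allocation.** Under Identification and selection of retirement villages, "The geographical locations (northeast or southwest) will be randomised to intervention group", and the other region becomes the usual care group (UCG). Each arm has five villages, chosen by convenience. No matching or stratification on resident mix is stated.
- **Baseline data.** Under Baseline data collection, the questionnaire records medicine use and "medication-related risk factors and eligibility for HMR" in both arms. Meeting one or more of the brochure criteria makes a participant eligible for an HMR.
- **Intervention.** In the Pharmacist Intervention Group (PIG), "Participants identified as having one or more medication risk factors will be referred to their GP".

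**The concern.** In a trial that randomises many units, differences in resident mix are chance noise and the standard error covers them. Here two regions are randomised, one to each arm. Whatever mix each region's villages and volunteers have stays a fixed feature of the contrast, and a larger sample does not average it out.

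The protocol itself ties its risk factors to uptake, through eligibility in both arms and referral in the PIG. They are measured in both arms before the intervention, so the measured part of any imbalance could be removed without new data. The stated plan leaves it in. A baseline significance test does not correct the effect estimate, and the plan states no action if such a test is positive. At stake is how far the reported difference reflects PHARMER rather than the share of referable residents in each region.

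**Working it through.** **Inputs from the Protocol article (Sample size; villages from Identification and selection).** UCG uptake 3% and PIG uptake 20% at six months; two-sided alpha 0.05; 80% power; 55 per group, raised to 77 for 20% drop-out and 20% clustering; five villages per arm.

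**The plan's own figure.** With pooled variance and no continuity correction, mean proportion 0.115:
n = [1.96·√(2·0.115·0.885) + 0.8416·√(0.03·0.97 + 0.20·0.80)]² / 0.17² = (0.884 + 0.366)² / 0.0289 = 54.1, so 55. The stated figure is reproduced. 77 = 55 × 1.40.

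**Bias from resident mix.** The documents give no uptake by risk status, so this is an assumption: uptake occurs only in at-risk residents, and 75% are at risk on average. Uptake among at-risk residents is then 0.20/0.75 = 0.267 (PIG) and 0.03/0.75 = 0.040 (UCG).

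| At risk, PIG / UCG | Crude difference |
|---|---|
| 75% / 75% | 0.200 − 0.030 = 17.0 points |
| 70% / 80% | 0.187 − 0.032 = 15.5 points |
| 80% / 70% | 0.213 − 0.028 = 18.5 points |
| 65% / 85% | 0.173 − 0.034 = 13.9 points |
| 85% / 65% | 0.227 − 0.026 = 20.1 points |

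With a higher average share, 85%, the same 20-point gap (75%/95%) matters a little less: 0.176 − 0.034 = 14.3 points, or 0.224 − 0.026 = 19.7 points.

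A second assumption gives a wider range: a risk factor with 50% prevalence that multiplies uptake by RR = 2 to 5, and a prevalence gap Δ of 10 to 30 points. Bias = p/(0.5·RR + 0.5)·(RR − 1)·Δ. At p = 20% this runs from 1.3 points (RR 2, Δ 0.1) to 8.0 points (RR 5, Δ 0.3). At p = 3% it runs from 0.2 to 1.2 points.

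**With no intervention effect.** At 4% uptake among at-risk residents in both arms, an 85%/65% split gives 3.4% v 2.6%, a spurious 0.8 points.

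**What two-stage adjustment does under the first assumption.** Take PIG 65%, UCG 85%. The first stage, without arm, gives pooled at-risk uptake (0.1733 + 0.0340)/(0.65 + 0.85) = 0.138. Expected uptake is 0.0898 (PIG) and 0.1175 (UCG). Observed minus expected differs by (0.1733 − 0.0898) − (0.0340 − 0.1175) = 16.7 points. The reverse split also gives 16.7. Most of the distortion is removed.

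**Precision.** With at-risk share s, the variance reduction for a fixed mix is s(1 − s)[(0.20/s)² + (0.03/s)²] / (0.1600 + 0.0291) = 0.216·(1 − s)/s: 11.6% (s = 0.65), 7.2% (0.75), 3.8% (0.85), 1.1% (0.95). If the mix is treated as sampled, half the between-stratum variance of the effect, ½·0.17²·(1 − s)/s, must be added back. The reduction falls to 0.140·(1 − s)/s: 7.5%, 4.7%, 2.5% and 0.7%. Under the second assumption it is 1.6% to 6.2%, which turns 55 per arm into 54.1 to 51.6.

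**Power of the baseline tests.** At 77 per arm, ignoring clustering, a two-sided test detects 65% v 75% at risk with power 27%, 65% v 80% with 55%, and 65% v 85% with 82%.

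**Events available.** Completers per arm: 77 × 0.8 = 61.6. Expected HMRs: 61.6 × 0.20 + 61.6 × 0.03 = 12.3 + 1.8, about 14.

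**The case against.** A fair opponent has several good points.

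- **An unadjusted primary test is a legitimate choice, and adjusted analyses are often left to an analysis plan.** True in general. Here, however, the protocol names the primary test, and with one region per arm the usual defence of a crude comparison, that randomisation balances mix on average over many units, is weak.
- **Risk status may not predict uptake strongly.** This stands. The documents show that risk factors gate eligibility and PIG referral; they do not rank predictors. In the survey cited in the Background, only 6% of at-risk residents had had an HMR in the previous year. That uptake occurs only in at-risk residents is an assumption made here for scale.
- **The mix is already narrowed.** This also stands. Entry requires three or more prescribed medicines, and one item of a 16-item checklist is enough to count as at risk. The at-risk share may well exceed the survey's 65%, which leaves less room for a 20-point gap. No figure in the documents supports a gap of that size.
- **A village-level comparison widens the interval.** Correct. Ten villages in two arms leave 8 degrees of freedom and a critical value of 2.306 instead of 1.96; (2.306/1.96)² = 1.38, more than any variance gained by adjustment.
- **Ignoring village clustering is the larger fault in the same sentence.** With 77/5 = 15.4 residents per village and an assumed intracluster correlation of 0.01 to 0.10, the design effect is 1.14 to 2.44 and the true type I error of the chi-square test is about 6.7% to 21%. That is a separate point and does not displace this one; a village-level comparison serves both.

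A reader might infer that the crude test wastes much power. The figures do not support that: the gain from adjustment is a few participants per arm at most on the second assumption.

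**Conclusion.** The point holds as one about bias from measured resident mix. The primary comparison is fixed as crude, the arms are single regions with convenience villages, and a risk measure that the protocol ties to uptake is collected in both arms but not used in the estimate. Under the stated assumption, a 65%/85% split shifts the 17.0-point difference by about 3 points either way, and a 70%/80% split by about 1.5. The precision gain, 1% to 12% of variance at most, is incidental.

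Two stronger readings should be resisted. A reader might infer that imbalance in risk could produce the planned effect by itself. Neither assumption gives that: the spurious difference with no intervention effect is 0.8 points on the first, and 8.0 points is the extreme of the second. A reader might also infer that adjustment makes the regions comparable. It cannot. Region and arm are the same contrast, so unmeasured regional differences, such as GP or pharmacist supply, stay fully confounded with PHARMER.

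**What to change.** In the Data analysis section, make the six-month primary comparison adjusted for one pre-named covariate: the number of HMR-brochure risk factors on the baseline questionnaire. Take it from that questionnaire in both arms, not from the checklist completed after the education session, which exists only in the PIG.

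Use a two-stage analysis. First, regress uptake on the covariate without an arm term. Then compare village-level observed minus expected uptake between arms. Keep the crude difference as a supportive result. Replace the baseline significance tests with summaries by arm and by village.

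The cost is wording and a little analysis; no new data are needed. State three limits with the change:

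- About 14 expected events allow one covariate, two at most. The number of medicines is a poor second choice, because use of five or more medicines is itself listed as a risk factor in the Background.
- The comparison rests on 8 degrees of freedom, so its interval will be wider than the crude one.
- Adjustment does not separate PHARMER from unmeasured differences between the regions.

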The reasons for the poor uptake of HMR among retirement village residents have been investigated by our team, and interventions for increasing the uptake of HMR in this group have been developed with input from stakeholders including retirement village residents, medical, pharmacy and allied health professionals [9]. A multi-faceted interventional approach targeting residents and their health professionals, such as educating residents regarding their risk factors and benefits of HMR, and notifying GPs of residents at risk of medication misadventure using a risk assessment checklist, have been recommended by stakeholders to increase the uptake of HMR in retirement village residents [9].

The **P**harmacist-conducted **H**MR to **A**ddress the **R**isk of **M**edication-related **E**vents in **R**etirement Villages (PHARMER) trial aims to test the effectiveness of a new multi-component intervention delivered by a pharmacist to increase the uptake of HMR among retirement village residents (primary aim), and to improve residents' adherence to medications (secondary aim). The hypothesis is that residents receiving the intervention are more likely to receive a HMR compared to their counterparts receiving usual care, leading to higher HMR uptake at three and six months from baseline.

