### Recruitment of participants

Participants will be residents living in participating retirement villages, recruited with the help of RLOs and village managers. Residents will be recruited using a range of strategies, which include:

• distributing invitation forms to all residents in each village;

• displaying a poster on the notice board or in the common area of each village; and

• advertising the study in the villages' newsletters and/or on the villages' multi-screen televisions (where available).

Residents who are interested in the study will be asked to complete the invitation form and return it to the study investigators using a provided reply-paid envelope, or to contact the study investigators. The invitation form includes questions that ask for the resident's name and contact details, and assess their eligibility for participating in the study. Returned invitation forms will be used to identify and select residents who are eligible for the study. Eligible residents will be invited to participate in the study over telephone. Those who are interested in participating after this initial discussion will be sent a plain language statement, a consent form and a questionnaire. They will be asked to complete the consent form and questionnaire, and return them to the investigators. Once written consent is obtained, eligible residents will be enrolled in the trial and allocated to either PIG or UCG depending on the location of the retirement village they live in.

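### Paired tests are named for a comparison of Morisky and SF-12 changes between two independent groups, which they cannot make

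*Protocol article*

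**What the plan says.** All statements are in the protocol article.

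- **Test and purpose (Data analysis).** "Paired samples t-test or Wilcoxon Signed-Rank test will be used to compare changes in Morisky scores", and the same sentence ends by applying the tests to "Health Survey scores between the two groups at six months".
- **Other tests (Data analysis).** Baseline characteristics in the two groups "will be compared using Chi-square, Mann-Whitney U or Student t-test". HMR uptake is compared by Chi-square test. Nothing else is named for Morisky or SF-12.
- **Who is compared (Recruitment of participants).** Residents are "allocated to either PIG or UCG depending on the location of the retirement village they live in". The villages of the two groups are at least 15 km apart (Identification and selection of retirement villages). No matching of residents is described.
- **Role of the outcome.** The Background gives improved adherence as the secondary aim, and Outcome measures states that the "secondary outcome measure will be participant self-reported medication adherence". SF-12 is collected at baseline and at six months but is not listed there as an outcome.
- **Scale (Baseline data collection).** "The total score on the Morisky scale ranges between 0 and 4; a score of less than 4 represents nonadherence".

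**The concern.** A paired t-test or a Wilcoxon signed-rank test needs two linked values per unit. A resident's baseline and six-month scores are linked; a PIG resident and a UCG resident are not. The sentence therefore names a method that cannot serve its own stated purpose.

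Followed literally, it leaves two options. One is to pair unrelated residents across arms, which is arbitrary. The other is to run the test separately in each arm. A within-arm change mixes any effect of the intervention with whatever would have happened anyway: trend over time, regression to the mean, and the effect of answering the same questionnaire twice. At stake is whether adherence, the secondary aim, gets a valid comparison of PIG with UCG.

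**Working it through.** **1. Can the named tests be read as a two-group comparison?** Setting the statements side by side:

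| Element | Protocol article | Consequence |
|---|---|---|
| Test | Paired t or signed-rank | Needs linked pairs |
| Contrast | PIG against UCG, change at six months | Two independent sets of change scores |
| Linkage between arms | None described | No pairs exist across arms |
| Two-sample tests | Student t, Mann-Whitney U | Named for baseline characteristics only |

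The only valid use of the named tests is baseline against six months within one arm. That estimates the mean change in PIG, or in UCG, and not the difference between the two.

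**2. The plan's own figure.** The article gives no effect size, SD or power for Morisky or SF-12. Its only figure is for HMR uptake, 3% against 20%, two-sided alpha 0.05, 80% power (Sample size). With the pooled-variance formula and no continuity correction:

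n = [1.96·√(2·0.115·0.885) + 0.842·√(0.03·0.97 + 0.20·0.80)]² / 0.17² ≈ 1.25² / 0.0289 ≈ 54.1, rounded up to 55.

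The stated 55 is reproduced, and 55 × 1.40 = 77 per arm. It serves here only to set a plausible number analysed: 77 × 0.80 = 61.6, about 62 per arm.

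**3. Size if a within-PIG result is read as a treatment effect.** Assumptions: n = 62 per arm, no true difference, normal change scores, independent residents, and a natural change d common to both arms, in SDs of the change score. The noncentrality of the within-arm test is d·√n:

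- d = 0.2: 0.2 × √62 = 1.57
- d = 0.3: 0.3 × √62 = 2.36

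With a critical t of about 2.00 on 61 degrees of freedom, the test is significant in about 34% and 64% of trials. A simulation of 20,000 trials per setting agrees, and gives the alternatives:

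| Shared change (SD) | PIG paired test significant | Exactly one arm significant | Two-sample test on changes |
|---|---|---|---|
| 0 | 5.1% | 9.7% | 5.2% |
| 0.2 | 34.0% | 44.9% | 5.0% |
| 0.3 | 63.9% | 45.8% | 4.9% |
| 0.5 | 97.3% | 5.2% | 4.9% |

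Reading significance in one arm but not the other as a difference can also miss a real effect. With a true difference of 0.5 SD and UCG improving by 0.3 SD, the two-sample test has 79% power. The pattern of PIG significant and UCG not appears in only 36% of trials.

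**4. Gain from baseline adjustment.** Take equal variances at the two times, correlation r, and the score variance as unit. The change score has variance 2(1 − r), and the six-month score adjusted for baseline has 1 − r². The ratio is (1 − r²) / [2(1 − r)] = (1 + r)/2:

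- r = 0.3: 0.65, a cut of 35%
- r = 0.5: 0.75, a cut of 25%
- r = 0.7: 0.85, a cut of 15%

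The change score is the right comparator, because changes are what the article plans to compare. The values of r are assumptions.

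**The case against.** **The sentence states a between-group purpose, so the investigators may simply have named the wrong test.** This has force. A reader might infer that the secondary aim will go untested, or that the control group will be discarded. The article does not support that: it plans a comparison of the two groups and collects both scores in both arms at both times. What it supports is narrower. The named tests cannot deliver the stated comparison, and no other test is named for adherence.

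**The 34% and 64% are not type I error rates of the plan.** This also stands. Within the PIG they are the power to detect a change that is real by assumption. They become false-positive rates only if that change is attributed to the intervention without reference to UCG, and the article does not say that it will be. The size also depends strongly on the decision rule and on the assumed change: the exactly-one-arm rule runs from 5.2% to 45.8% over the range shown.

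**A condensed article leaves detail to an analysis plan.** This does not answer the point. A test is stated and it is the wrong kind; nothing is merely omitted. The same section names suitable two-sample tests, but assigns them to baseline characteristics only.

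**The matter is secondary.** Correct as to scope. HMR uptake, its Chi-square test and the sample size do not depend on this sentence, and SF-12 is an additional measure rather than a listed outcome.

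**Conclusion.** The sentence is wrong as written. It assigns tests for paired data to a contrast between independent, unmatched groups, and the only listed secondary outcome has no valid between-group test in the article. That conclusion follows from the text and needs no numerical assumption.

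The numerical harm is conditional. With 62 residents per arm, no true effect, a shared change of 0.2 or 0.3 SD of the change score, and a significant PIG change read as a treatment effect, the false conclusion arises in about 34% or 64% of trials. A two-sample test on the changes stays at about 5%. The shared change, the normal scores and the independence of residents are all assumptions.

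The error is confined to adherence and, as an additional measure, SF-12. It can be corrected before analysis.

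**What to change.** **Essential.** Replace the sentence so that the change from baseline to six months in Morisky, PCS and MCS scores is compared between PIG and UCG by an independent-samples t-test or Mann-Whitney U test. Both are already named in the Data analysis section.

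**Preferable.** Model the six-month score on arm and baseline score, for the lower residual variance shown above. This is a gain in precision; the two-sample test on changes already corrects the mismatch.

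**Paired tests.** If kept, label them as descriptive within-arm results from which no treatment effect is inferred.

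**Cost.** Wording only. Both scores are already collected in both arms at both times, and the sample size does not change.

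**Not resolved by this change.** A two-sample test or a baseline-adjusted model still ignores clustering by village. Adding a village-level correction would not separate the effect of arm from that of region, because only two regions are randomised, one to each arm. Those points need their own treatment.
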